### Statistical analysis

2.6

Descriptive and exploratory analyses will be performed, and normality will be assessed using the Kolmogorov–Smirnov or Shapiro–Wilk tests, and if necessary, the data will be transformed for normalization. The differences between the baseline groups will be explored using one-way analysis of variance (ANOVA) or Kruskal-Wallis tests for continuous data and chi-square tests for categorical data.

The intention-to-treat principle will be used for the primary outcome analysis. The main analyses will employ random coefficient linear mixed models for normally distributed endpoints or generalized mixed models for non-normally distributed endpoints. Post-hoc analysis with Bonferroni correction will assess differences between treatment factors. Cohen’s d will be used to indicate the effect size, and significance will be set at *p* < 0.05.

Fecal samples will undergo taxonomic analysis, grouped into amplicon sequence variants (ASVs), and summarized at different taxonomic levels. These data will be imported in R for use with the Phyloseq package. Several indices of alpha and beta diversity will be evaluated (i.e., Simpson Index, Shannon-Wiener Index, Bray–Curtis dissimilarity, Unweighted and weighted Uni-Frac for beta-diversity). Principal Coordinate Analysis (PCoA) will be performed to visualize the dissimilarity matrix between all samples and a PERMANOVA on exercise groups will be performed. Analysis of Compositions of Microbiomes (ANCOM) with bias correction will be used to test for differential abundance of individual ASVs at several levels to compare the three exercise groups. We will use the Benjamin– Hochberg corrected significance level of 0.05 to minimize false discovery rate (FDR). For the metabolomics analysis, samples will be normalized by the total ion current and means centered using Pareto scaling. Univariate analysis of variance will be performed on data from both ion modes to identify variations in peak areas between groups at baseline and after the 12-weeks intervention. Partial least squares discriminant analysis (PLS-DA) will be used to detect the most critical discriminant metabolites in each comparison across groups consistent with published guidelines for metabolomics trials (36). Microsoft packages (e.g., Excell), SPSS (version 27) and R (version 4.2.) software will be used to manage and analyze the different data.

The study primary null hypothesis are: (a) there are no differences in *Faecalibacterium prausnitzii* and other SCFA-producing bacteria after the intervention between groups; (b) there are no differences in *Faecalibacterium prausnitzii* and the other SCFA-producing bacteria after the intervention between the RES + AER group versus the AER group; (c) there are no differences in *Faecalibacterium prausnitzii* and other SCFA-producing bacteria after the intervention between the RES + AER group vs. the RES group. We hypothesize that combining AT and RT will have a greater impact on the GM composition, specifically in increasing the relative abundance of *Faecalibacterium prausnitzii* and other SCFA producing bacterial strains, an increase in skeletal muscle mass and strength, as well as enhanced physical performance measures in the concurrent exercise training group.

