**Methods:**

This pilot single center three-arm parallel open-label randomized control trial (RCT) will randomly assign eligible participants to: (i) moderate aerobic exercise (AER); (ii) resistance exercise (RES); or (iii) concurrent exercise training (RES + AER). Participants will engage in a supervised center-based exercise intervention (12-weeks, 3 d/week, 60 min/d), and will be assessed at (i) baseline, (ii) end of intervention (14 weeks), and (iii) at close-out (26-weeks). The primary outcome will be the change in the relative abundance of *Faecalibacterium prausnitzii* and other short-chain fatty acid producing bacteria after the intervention (14-weeks). A set of complementary outcomes will also be assessed to broadly characterize the impact of each exercise intervention on body composition, skeletal muscle function, functional performance and general GM composition.

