The effect of exercise on the GM composition has been analyzed qualitatively and quantitatively and is mostly associated with positive results in the aging process (18, 19). For instance, the increase in exercise levels is associated with a decrease in the relative abundance of potentially pathogenic taxa, higher microbiota biodiversity and butyrate production taxa (18), whereas a sedentary behavior is associated with gut dysbiosis, growth of pathogenic opportunists bacteria strains and alterations on GM functionality (20). Higher proportions of *Akkermansia, Faecalibacterium prausznitzii, Roseburia hominis*, and *Bifidobacterium spp*- known for its anti-inflammatory health benefits were observed in active women and athletes (14). Further, exercise training decreased the abundance of bacteria associated with intestinal dysbiosis, suggesting that exercise stimulates healthy gut microbes, in addition to improving muscle in physically active individuals (1). Despite these positive effects of exercise training on GM in young adults, the findings in older adults are less clear and conflicting, changes appear to be transient and reversible and to date, the effects of exercise training on GM in patients with sarcopenia remains unclear (21, 22).

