### Intervention

2.3

The exercise intervention will be carried out in the city of Famalicão, 3 days/week, 60 min/day, on pavilions and at municipal gyms whereas the assessment procedures will take place at Faculty of Sport at the University of Porto, since the institution has specific facilities and equipment for this purpose. The intervention length is 12-weeks followed by one washout period of 12-weeks. The expected total study duration is ~8 months, including the baseline and the close-out procedures (Figure 1). The exercise sessions will take place in the morning, on alternating days of the week and will be supervised by experienced exercise physiologists. The sessions consist of a warm-up (5 min), a main part (50 min) and a cooldown (5 min). The warm-up and cooldown will be identical in all three groups, with only the main part being different between the groups.

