### Assessments

2.5

Participants will be evaluated in three different moments: (i) baseline; (ii) end of the intervention (12 weeks); (iii) close-out (24 weeks). The study has a total duration of 26 weeks. In each study visit, participants will perform the same physical and functional assessments, body composition analysis, and provide a fasting blood and feces sample. Other confounding variables will also be recorded, including nutritional intake (through a 3-day diary), daily PA levels (through a PA tracker), medication intake. Medication and supplementation along with other associated comorbidities will be assessed using a medical questionnaire and medication history questionnaire. Considering the study design, the following outcomes will also be evaluated: (a) retention and attrition rates; (b) adherence to exercise intervention; (c) safety; (d) intervention effect on dependent outcomes (Table 4).

**Table 4 tab4:** Overview of the assessment visits and data collection at each visit.

Study phase	Pre-randomization		Intervention		Follow-up
Visit description	Screening	Baseline	Start	End	CO
Visit number	1	2	3	4	5
Week number	−2	0	2	14	26
Informed consent, review inclusion/exclusion criteria	x				
Demographic information, medical history, medication use	x				
IPAQ questionnaire	x				
Office blood pressure	x	x	x	x	x
Anthropometry measurements	x	x		x	x
Randomization	x				
Body composition (DEXA)		x		x	x
Blood and fecal samples for study assays		x		x	x
Nutritional Intake		x		x	x
Skeletal muscle strength		x		x	x
Physical performance testing		x		x	x
Daily physical activity		x	x	x	x
Assess adverse events			x	x	x
Exercise intervention			x	x	

CO, close-out.

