A recent review summarizing data from interventional and observational studies on older adults (where sarcopenia was more prevalent) indicated that exercise and physical activity can have a beneficial impact on the GM composition (19) but due to methodological and sampling disparities, it was not possible to reach a consensus on which taxa was most responsive/influenced by exercise. Further, growing evidence shows that different exercise training modalities (type, frequency, duration, and intensity) may elicit different GM composition phenotypes and skeletal muscle health outcomes (18). Propionate and butyrate, both gut-derived SCFA metabolites, can act as adenosine monophosphate-activated protein kinase (AMPK) activators and stimulate peroxisome proliferator-activated receptor-gamma coactivator 1 alpha isoform (PGC-1α) and insulin/Insulin-like Growth Factor 1 (IGF-1) signaling, promoting muscle biogenesis, whereas its decrease has physiological consequences like reduction in the mitochondrial fatty acids’ oxidation, increased intramuscular fatty acid deposition and insulin resistance (1, 11). Thus, given that different exercise training regimens differently impact the body, we can hypothesize that each regimen promotes distinct alterations on GM composition. RES may enhance bacterial strains associated to muscle strength while AER may promote the increase on the relative abundance of taxa associated to aerobic capacity and SCFA production whereas the combination of both forms of exercise (resistance + aerobic) may lead to an added effect. Furthermore, with this study we will be able to shed light on the (ir)reversibility of the preliminary results, evaluate the adequacy of our primary outcome and analyze the effect of our intervention. The findings collect on the washout period will be important to investigate GM resilience (i.e., the ability or process of the GM to withstand exercise benefits and/or manage everyday challenges) and specifically, explore whether these changes induced by exercise are sustained over time or not in the three different exercise regimens.

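### Read in its usual sense, the named random coefficient model does not estimate the end-of-intervention group difference that the protocol makes primary

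*Protocol article*

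**What the plan says.** **Model.** Protocol article, 2.6 Statistical analysis: "The main analyses will employ random coefficient linear mixed models for normally distributed endpoints", continuing "or generalized mixed models for non-normally distributed endpoints". Data may be transformed towards normality where needed. The section does not give the time coding, the random coefficients, or the visits that enter the primary model.

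**Primary question.** Section 2.4.1 makes the change in relative abundance of *F. prausnitzii* and other SCFA producers after the intervention primary. It lists *F. prausnitzii* at close-out separately, as secondary. The first null hypothesis in 2.6 denies a difference in *F. prausnitzii* "and other SCFA-producing bacteria after the intervention between groups". The other two say the same for concurrent training against each single modality.

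**Third visit.** Section 2.3: "The intervention length is 12-weeks followed by one washout period of 12-weeks". The Discussion says that this period will serve to "explore whether these changes induced by exercise are sustained over time or not". The Introduction says of earlier work in older adults that "changes appear to be transient and reversible".

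**Visit times.** The abstract gives "i) baseline, (ii) end of intervention (14 weeks), and (iii) at close-out (26-weeks"; section 2.5 gives "i) baseline; (ii) end of the intervention (12 weeks); (iii) close-out (24 weeks". Table 4 puts baseline at week 0 and the start of exercise at week 2, so the two sets may differ only in their origin.

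**The concern.** A straight line through three visits cannot represent a gain followed by a loss, or a gain followed by a plateau. The visit that defines the primary outcome is the middle one, and the middle point of a roughly equally spaced series carries next to no weight in a slope. A group-by-slope test would therefore answer something close to the secondary close-out question.

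Two things are at stake. The first is power, if the effect wanes during washout. The second is the size of the estimate, which is distorted even if nothing wanes. Section 2.4.1 says that the pilot data will refine the sample size of a full-scale trial. Required sample size goes with 1/d², so an effect read at half its true size, with the same SD, would make that trial about four times too large (1/0.5² = 4).

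**Working it through.** **Inputs.** d = 0.9, 80% power, two-sided 0.05 and 21 per group (2.2.2); visit times 0/14/26 (abstract, Table 4) or 0/12/24 (2.5). Assumptions, not in the document: d is in units of the SD of change from baseline; compound symmetry; complete data; a single pairwise comparison without the Bonferroni step, as in the sample-size section.

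**1. The plan's own figure.** A two-sample t-test has noncentrality 0.9 × √(21/2) = 2.916 on 40 degrees of freedom. Power is 0.812 at 21 per group and 0.792 at 20, so 21 reproduces. It fits a direct two-group comparison at one time point.

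**2. Weight of each visit in the slope.** With complete, balanced data, the group-by-time effect of a random intercept and slope model equals the difference in mean least-squares slopes: b = Σ(t − t̄)·effect / Σ(t − t̄)².

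- 0/14/26: t̄ = 13.33; deviations −13.33, +0.67, +12.67; sum of squares 338.67.
- 0/12/24: t̄ = 12; deviations −12, 0, +12; sum of squares 288.

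The end-of-intervention visit has almost no weight on the first schedule and none on the second.

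**3. Implied end-of-intervention effect.** Let the true pattern be (0, 1, r), where r is the share of the gain kept at close-out. Multiply the slope by the time to end of intervention.

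- 0/14/26: 14 × (0.667 + 12.667r)/338.67 = 0.551 (r = 1), 0.289 (r = 0.5), 0.028 (r = 0).
- 0/12/24: 12 × 12r/288 = 0.5r = 0.50, 0.25, 0.

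**4. Power of the slope test.** If the SD of change is 1, the within-person residual variance is 0.5, whatever the correlation. The standardised slope effect is 0.9 × (weighted sum)/√(0.5 × sum of squares).

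- 0/14/26: √(0.5 × 338.67) = 13.01. The effect is 0.9 × 13.333/13.01 = 0.922, 0.9 × 7.0/13.01 = 0.484 and 0.9 × 0.667/13.01 = 0.046.
- 0/12/24: √(0.5 × 288) = 12. The effect is 0.9r = 0.90, 0.45 and 0.

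| Share kept at close-out | Implied effect, % of truth | Slope-test power | Direct contrast power |
|---|---|---|---|
| 100% | 50–55 | 81–83% | 81% |
| 50% | 25–29 | 29–34% | 81% |
| 0% | 0–3 | 5% | 81% |

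Simulation (20,000 trials per scenario, within-person correlation 0.3, 0.5 and 0.7) gave these powers; the correlation made no material difference.

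**5. A milder way of reading the fit.** One could instead read off the fitted difference in level at the middle visit, which lets the line absorb part of the effect as a baseline difference. On 0/14/26 this gives 0.624, 0.462 and 0.301 SD against a true 0.9 (69%, 51%, 33%). It is still attenuated.

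**6. Would using only two visits rescue the named model?** Two visits supply three covariance elements (two variances, one covariance). Random intercept, random slope, their covariance and a residual need four. The full random coefficient model is not identifiable on two visits, so in its ordinary sense it needs the close-out visit.

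**The case against.** The strongest reply is that the straight line is inferred. In a linear mixed model, linear means linear in the parameters. A random slope concerns the random part, and the fixed part could still hold categorical visit with group-by-visit terms, which would avoid the problem. Sections 2.4.1 and 2.6 already fix the primary time point, so a reading compatible with them exists, and a statistical analysis plan not shown here may adopt it. This stands as a limit on certainty. It does not remove the point: the article commits to a named model class whose ordinary form leads away from its own null hypotheses.

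Three stronger readings are tempting, and the document does not support them.

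- *That the protocol expects the effect to reverse.* The Introduction reports reversibility from earlier work, which it also calls unclear and conflicting. The Discussion treats persistence in this trial as an open question. The 5% power figure needs full reversal; with full retention the slope test loses no power, and only the estimate is attenuated.
- *That every analysis of the primary outcome is affected.* Only the normal-endpoint branch carries the random coefficient wording. A relative abundance may fall in the other branch, although transformation could bring it into this one.
- *That the plan wastes the baseline measurement.* This would argue from silence. Section 2.6 is not exhaustive on covariates: section 2.3 names physical activity as one that 2.6 does not repeat.

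**Conclusion.** The point holds conditionally. If the random coefficient model is fitted in its usual form over the three visits, its group-by-time coefficient is not the primary contrast. The attenuation of the effect, to about half at best, does not depend on reversal. The loss of power does: none with full retention, severe with half, and down to the significance level with full reversal. The percentages of the true effect follow from the visit times alone. The power figures also rest on the assumed SD-of-change units, compound symmetry and complete data. Because the time coding is unstated, this is a risk in the plan as written and not a demonstrated loss, but it can be removed at almost no cost.

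**What to change.** For the primary analysis, replace the random coefficient model with a repeated-measures mixed model: visit as a categorical factor (baseline, end of intervention, close-out), group, group-by-visit and an unstructured within-person covariance. Name the end-of-intervention group contrasts, matching the three stated null hypotheses, as primary and the close-out contrasts as secondary. State the same categorical-visit structure for the generalized mixed model branch. Reconcile the 12/24-week and 14/26-week labels to one origin. A common baseline mean, or baseline as a covariate, is an optional gain in precision.

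The cost is a change of wording, with the same data and software. The model needs a few more parameters: nine group-by-visit means instead of six intercepts and slopes (3 more), and six covariance parameters instead of four (2 more).

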The available evidence suggests that different types of exercise modalities may elicit distinct alterations in GM composition. Aerobic and resistance exercise activate different molecular pathways. Aerobic training (AER) improves the permeability of intestinal barrier, promotes bacterial taxa related to aerobic capacity and SCFA production whereas resistance exercise (RES) may enhance the composition of bacterial strains associated to muscle strength, upregulate anti-inflammatory cytokines and reduce endotoxemia (18, 23, 24). Given that these two exercise training regimens activate different bioenergetic signaling pathways [i.e., AER- activates the transient activated protein kinase (AMPK) pathway whereas RES activates the longer-lasting mechanistic target of rapamycin (mTOR)], we can hypothesize that each regimen promotes distinct alterations on GM, whereas the combination of both forms of exercise (resistance + aerobic) may lead to a complementary or added effect. There is limited evidence on the effects of concurrent training on sarcopenia outcomes, but the scarce evidence highlights the positive effects of combining both forms of exercise training on body composition, skeletal muscle regeneration and cardiorespiratory fitness (25). However, to date, no studies specifically analyzed the impact of different exercise training regimens (i.e., resistance, aerobic and concurrent exercise training) on GM composition and investigated its effects on skeletal muscle mass and function in older adults with sarcopenia. Thus, we designed a pilot three-arm randomized controlled trial (RCT) to unravel the effect of these exercise regimens on GM to help clarify the optimal exercise mode to manage sarcopenia and, we hypothesize that the combined exercise training mode may elicit more benefits on GM composition and function, on gut health and physical performance than each exercise training regimen alone.

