*In summary*, with this study we expect to create a consecutive line of research to fill a current literature gap and explore the impact of three different exercise regimens on GM composition and gut-derived metabolites in older adults with sarcopenia. These findings may help clinical guidance and enhance exercise prescription in this high-risk population. For instance, if confirmed that RES + AER are the optimal mode of exercise training to modulate GM composition and improve skeletal muscle health, clinicians and exercise specialists may prioritize it in patients with sarcopenia with certain GM composition phenotypes. Lastly, our study will contribute with an evidence-based approach, to a deeper understanding on the optimal exercise mode to elicit gut and skeletal muscle health benefits. Therefore, our study could have clinical meaningful implications and impact patient’s quality of life and lifespan.

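### The hypothesis that concurrent training beats each single mode needs both pairwise primary nulls rejected, but section 2.6 lists three parallel nulls and a Bonferroni step that costs this joint claim power for no needed error control

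*Protocol article*

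**What the plan says.** The Introduction states this hypothesis: "combined exercise training mode may elicit more benefits on GM composition and function, on gut health and physical performance than each exercise training regimen alone". Section 2.6 (Statistical analysis) repeats the direction: "We hypothesize that combining AT and RT will have a greater impact on the GM composition".

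The formal hypotheses in section 2.6 begin "The study primary null hypothesis are: (a) there are no differences in" and are three statements of no difference in *F. prausnitzii* and other SCFA producers after the intervention: (a) between the groups, (b) RES + AER versus AER, (c) RES + AER versus RES. All three are called primary, none is directional, and no combination of them is tied to the hypothesis.

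On multiplicity, section 2.6 says "Post-hoc analysis with Bonferroni correction will assess differences between treatment factors", with overall significance at p < 0.05. It does not say whether two or three comparisons are counted.

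The Discussion considers what clinicians might do "if confirmed that RES + AER are the optimal mode of exercise training to modulate GM composition and improve skeletal muscle health".

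Section 2.2.2 (Sample size) gives d = 0.9 on *F. prausnitzii* between groups, 80% power and two-sided 0.05, hence 21 per group, raised to 23 per group (N = 69) for 10% attrition.

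**The concern.** Being better than each single mode is a claim about two contrasts together. Three parallel primary nulls lead to three different conclusions: that the arms differ somewhere, that concurrent training differs from one mode, or that it beats both. Only the third is the stated hypothesis. Null (a) can be rejected because AER and RES differ, with concurrent training no better than one of them. Null (b) or (c) alone leaves the other comparison open.

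The correction does not match the claim either. Bonferroni protects against an error when any one rejection is enough. When both tests must succeed, it lowers power and protects against nothing that the both-required rule does not already cover. At stake are a clear reading of the primary result and 11 to 18 percentage points of power for the hypothesis that the article puts forward.

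**Working it through.** **Inputs.** From section 2.2.2: d = 0.9, two-sided 0.05, 80% power, 21 analysed per group. From section 2.6: nulls (a) to (c), Bonferroni, p < 0.05. Assumed: normal outcome, common SD, and d = 0.9 for RES + AER over *both* other arms (the article gives a single d). The Bonferroni family is not stated, so 2 and 3 are both shown.

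**1. The plan's own figure.** A two-sample t-test with d = 0.9, two-sided 0.05 and 80% power needs 20.4, so 21 per group. At 21 per group its power is 81.2%. The stated 21 is reproduced, for one pairwise comparison at unadjusted 0.05.

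**2. Error of the both-required rule.** The joint claim is false if RES + AER fails to beat at least one mode. That contrast must still be rejected in favour of RES + AER, so

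P(false joint claim) ≤ P(reject the true null in that direction) ≤ 0.05/2 = 0.025.

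This holds whatever the other contrast does. In simulation with RES + AER equal to one mode and 2.5 SD above the other, the rate was 2.5%. No further correction is needed for this claim.

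**3. Power for the joint claim.** Three normal arms of 21, pooled variance (df = 3 × 20 = 60), RES + AER 0.9 SD above both. Each contrast is t = (difference in means)/(s√(2/21)), with noncentrality 0.9 × √(21/2) = 2.92. The two contrasts share the RES + AER arm (correlation 0.5). At least 200,000 simulated trials per scenario:

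| Level per test | One given contrast significant | Both significant | Exactly one significant |
|---|---|---|---|
| 0.05 | 82% | 71% | 21% |
| 0.05/2 | 73% | 60% | 26% |
| 0.05/3 | 67% | 53% | 29% |

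Bonferroni therefore costs the joint claim 71 − 60 = 11 points (family of two) or 71 − 53 = 18 points (family of three).

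**4. Sample size equivalent.** For 80% power on both contrasts, about 25 per group would have to be analysed at 0.05 each, 30 at 0.05/2 and 33 at 0.05/3.

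**5. Why (a) or one contrast is not enough (illustration only).** Suppose RES + AER equals RES and both exceed AER by 0.9 SD. Null (a) is then rejected in about 84% of trials, and at least one of (b) and (c) favours RES + AER at 0.05/3 in about 68%. These are not error rates: (a) and (b) are truly false here, and almost all of these rejections detect a real difference. They show that such results are expected even when concurrent training adds nothing over RES. Both (b) and (c) at 0.05 are won in about 2.5%.

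**6. Error of the rule proposed under the fix.** The rule is both at 0.05, or one alone at 0.025. With all arms equal, a rerun of the simulation (1,000,000 trials) gives at least one rejection of (b) or (c) in about 4.8% of trials counting either direction, and in about 2.4% counting only results in favour of RES + AER.

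**The case against.** The strongest reply is that each null has its own content and can be reported for what it says, and that Bonferroni is correct for (b) and (c) as two separate claims. This stands, and it rules out several stronger readings.

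- A reader might infer that Bonferroni is an error here. It is not; it is only stricter than the joint claim needs.
- A reader might take the 84% and 68% as false-positive rates. They are rejections of nulls that are false in that scenario, and become misleading only if reported as support for the joint claim. No passage says they will be; the Discussion sentence is conditional and is not an analysis rule.
- A reader might say that rejecting exactly one of (b) and (c) leaves the plan without a conclusion. The separate nulls do supply one: a difference from that mode, and none shown from the other.
- A reader might quote 53% as the plan's power. That presumes a family of three, which the article does not state; with two it is 60%.

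It can also be said that a testing hierarchy belongs in an analysis plan not shown here, that the word post-hoc suggests (a) first and pairwise tests second, and that this is a pilot. On the first, the article itself fixes the primary nulls, the correction and the hypothesis, and the mismatch is among those. On the second, no gate is written, and passing (a) first would not make one pairwise result establish superiority to both. The third lowers the stakes, since section 2.4.1 says the data will help refine a larger trial. But the article also sets a powered primary comparison and speaks of confirming an optimal mode.

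**Conclusion.** The point holds in a limited form. The stated hypothesis requires (b) and (c) both to be rejected in favour of RES + AER. Section 2.6 does not tie its three parallel, non-directional nulls to that requirement, and its Bonferroni step is needlessly conservative for the joint claim: about 71% power without it, against 60% or 53% with it.

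The percentages rest on normal data, equal SDs, 21 analysed per arm, simple pairwise tests in place of the planned mixed models, and an effect of 0.9 SD over both arms. The logic and the 2.5% bound do not depend on the assumed effect. Dropping the correction does not bring the joint claim to 80% power; the 80% in section 2.2.2 belongs to one comparison.

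**What to change.** Add one decision rule to section 2.6, for *F. prausnitzii* at the end of the intervention (the measure on which the trial was sized):

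- Superiority of RES + AER to each single mode is concluded only if (b) and (c) are both significant at two-sided 0.05 in favour of RES + AER, with no further correction.
- If that is not met, superiority to one mode alone is claimed only if its contrast is significant at 0.025 (Bonferroni over two) in favour of RES + AER.
- Null (a) and the RES versus AER contrast are supportive.

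Word the Discussion's sentence on confirming RES + AER so that it refers to the first bullet. Fix the rule before outcome data are seen by group, so that it cannot be fitted to whichever contrast succeeds.

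The cost is wording; no participants or procedures change. The small downside is that one significant contrast, or a significant (a), no longer counts as support for the main hypothesis.
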